### Blood Metabolite Analysis

Briefly, 10 ml of blood will be collected in Becton Dickinson (BD) Vacutainer glass plasma tubes with either sodium heparin (366480, green closure) or sodium citrate (366415, blue closure) as an anticoagulant. Blood will be centrifuged at 2400 relative centrifugation force for 20 minutes at 4 °C to separate the plasma. Both the separated plasma and cell-culture medium will be stored at –80 °C. Before the analysis, precipitation of the plasma protein will be done by adding 200 μl of acetonitrile to 100 μl of a thawed plasma sample followed by vortexing. The solution will be then centrifuged at 18,000 relative centrifugation force at 4 °C for 10 minutes and the supernatant dried and reconstituted using 100 μL of water/methanol solution (95:5) containing 0.1% formic acid prior to 2 μL being injected and analyzed with HPLC/MS.

For HPLC/MS, the gradient is held for 1 minute at 5% mobile phase B, and it then progresses from 5% to 10% B over a period of 1 minute, 10% to 25% B over 2 minutes, 25% to 60% B over 2 minutes, and 60% to 95% B over 6 minutes, after which it is held at 95% B for 2 minutes, followed by washing and column equilibration steps. Mobile phase A uses water acidified with 0.1% formic acid, and mobile phase B uses 80% acetonitrile-water acidified with 0.1% formic acid. The mass spectrometry analyses will be performed using the targeted assay settings described above. Samples will then additionally be analyzed with untargeted methods developed for untargeted metabolomics [20-25].

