**Methods:**

This manuscript provides a rationale and a protocol for a clinical study and laboratory experiments to test the hypothesis. The methods have 3 key aspects. Phase 1 comprises optimization of assays of 5 key metabolites arising from CoA restriction, namely L-leucine, ketoisovalerate, ketodeoxycholate, oleic acid, and sphingosine-1-phosphate. Phase 2 comprises recruitment of patients to obtain serum samples to measure the metabolites, and phase 3 comprises culturing and treating trophoblast cells to induce CoA restriction and test the effects of the metabolites on the cells. Patients with preeclampsia and healthy controls will be recruited based on World Health Organization criteria for preeclampsia. Exclusion criteria include multiple pregnancies, premature rupture of membranes, and various medical complications. Blood samples will be collected and analyzed using high-performance liquid chromatography/mass spectrometry (HPLC/MS) to quantify key metabolites associated with CoA restriction. For trophoblast cell studies, BeWo cells will be cultured under conditions likely to induce CoA restriction, including hypoxia and human chorionic gonadotropin supplementation, and will also be treated with the key metabolites to determine what effect they might have. Cell viability, apoptosis, energy metabolism, and gene expression (focusing on genes involved in CoA synthesis and metabolism) will be assessed. Statistical analysis will involve 2-tailed *t* tests or Mann-Whitney *U* tests to compare metabolite concentrations between patients with preeclampsia and controls. A correlation matrix will be used to explore associations between metabolite levels and patient characteristics.

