### Aims of This Study

Prior work indicates that CoA levels are reduced in the first trimester of pregnancies, triggering the rise of harmful metabolites that later cause preeclampsia. It is extremely difficult to test this hypothesis by direct measurement of CoA concentration, because it is bound to many different metabolites and proteins, and obtaining a biopsy from the diseased part of a placenta would be difficult and highly invasive. However, the metabolites generated as a consequence of CoA restriction are readily detected using mass spectroscopy, even though they are a mixture of hydrophilic and hydrophobic molecules. Hence, this pilot study aims to uncover evidence supporting the CoA restriction hypothesis through 2 avenues. The first of these is to provide the proof of concept of a methodology to quantify the metabolites (specified in Figure 1) and then compare the levels in patients with preeclampsia versus matched controls. The second seeks to emulate the onset of CoA restriction in cultured cells.

Hence, this article outlines a 3-phase protocol (protocol version 1.1, May 23, 2024) for clinical samples and cell culture studies to screen for the indirect effects of CoA restriction (Figure 2). Initially, laboratory methods will be developed to quantify levels of the harmful metabolites in serum. Then, blood samples from patients with preeclampsia and matched controls will be taken to determine if the predicted harmful metabolites are elevated in patients with the disease. In parallel, trophoblast cells will be stressed to induce CoA restriction, and then investigated in 3 ways. The first will determine if the harmful metabolites appear in the cell culture medium, while the second will study the effect of these metabolites on otherwise healthy cells and the third will determine the expression level of genes known to be affected by the disease (ie, those described in the Placental Gene Expression Changes in Preeclampsia section) to determine if they have significantly changed.

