### Recruitment

Women with preeclampsia will be identified by the obstetricians collaborating with the study from the antenatal clinics and wards at Latifa Hospital in Dubai. Women with preeclampsia who meet the inclusion criteria outlined below will be approached verbally, asking if they would like to participate in this study. A patient information sheet will be provided, and after they provide written informed consent, they will be recruited into the study.

Baseline clinical and laboratory characteristics will be collected from the patients’ medical notes, including obstetric history, booking weight, height, renal and liver function, comorbidities, and smoking history. A data collection form has been designed for this purpose (Multimedia Appendix 1). The collected data will be anonymized and linked to samples by study ID only. Concurrent control participants will be identified following a review of the antenatal clinic lists to seek women with uncomplicated pregnancies who are undergoing routine antenatal care in the same antenatal clinic at Latifa Hospital in Dubai. Controls will be matched for approximate weight, age (5-year age group) and week of gestation. Control participants who meet the inclusion criteria outlined below will also be approached verbally, asking if they would like to participate in this study.

Patient blood samples will be taken at the time of routine phlebotomy for blood tests required as part of clinical care. As such, no adverse events specifically related to the study procedure are anticipated.

Blood samples will be collected in a heparinized EDTA (ethylenediaminetetraacetic acid) 10-ml container and transported immediately on ice to the laboratory for processing, as described in Blood Metabolite Analysis section below. One member of the research team has the responsibility for sample processing to ensure consistency. Metabolite measurements will be conducted by 2 members of the research team.

Preeclampsia will be defined as per the WHO Recommendations for Prevention and Treatment of Pre-eclampsia and Eclampsia [18]; specifically, the onset of a new episode of hypertension during pregnancy, characterized by persistent hypertension (diastolic blood pressure ≥90 mm Hg), and substantial proteinuria (>0.3 g/24 hours or more or a protein level of +2 or above in the urine dipstick test). The gestational week in which the sample is collected will be recorded for all women.

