### Data and Statistical Analysis

The patient metabolite-concentration data will be examined to determine differences between the preeclampsia and healthy patient samples and to determine if they follow normal distributions. If they do, paired and unpaired 2-tailed *t* tests will be carried out to determine if the concentrations are significantly different. If they are not, then the Mann-Whitney *U* test will be used. These same tests will be used for metabolite concentrations in the in vitro cell cultures. A correlation matrix will be calculated between the metabolite concentrations and patient characteristics, including weight, age, and week of gestation, to determine if there are any associations. In addition to the planned targeted analysis to test our hypothesis, the plasma metabolomes will also be measured with untargeted HPLC/MS, and the data will be analyzed using multiple-testing correction-adjusted *t* tests and partial least-squares discriminant analysis to identify which metabolites are altered by preeclampsia status. Pathway enrichment will be used to identify dysregulated pathways, which will then be compared with previously published data.

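### Two sections name incompatible blood tubes, and one leaves the anticoagulant open, so measured concentrations can differ between women by tube

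*Protocol article*

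**What the plan says.** Two sections of the protocol article describe the collection tube.

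- **Recruitment:** "Blood samples will be collected in a heparinized EDTA (ethylenediaminetetraacetic acid) 10-ml container". The same sentence refers to the Blood Metabolite Analysis section for processing.
- **Blood Metabolite Analysis:** tubes "with either sodium heparin (366480, green closure) or sodium citrate (366415, blue closure) as an anticoagulant". EDTA is not mentioned, although catalogue numbers and closure colours are given.

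The name of the matrix also varies. The abstract speaks of "recruitment of patients to obtain serum samples to measure the metabolites", and Aims of This Study says "laboratory methods will be developed to quantify levels of the harmful metabolites in serum". The laboratory method says "Blood will be centrifuged at 2400 relative centrifugation force for 20 minutes at 4 °C to separate the plasma", and Data and Statistical Analysis says "the plasma metabolomes will also be measured with untargeted HPLC/MS". Development of Targeted Metabolomic Assays sets extraction and quantification limits in a standard plasma matrix.

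Three other provisions bear on the point:

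- Matching is on approximate weight, age group and gestational week (Recruitment). The Power section adds type of pregnancy.
- One team member processes all samples.
- The group comparison uses t tests or the Mann-Whitney test, with no term for the tube.

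**The concern.** The two tube instructions cannot both be followed. The second also lets two women be sampled in different anticoagulants even when staff follow it exactly. Nothing else in the plan closes the gap: tube type is neither a matching factor nor an analysis term, and single-person processing begins after the tube has been filled.

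The study is meant to quantify concentrations accurately and to ask whether they are higher in preeclampsia. If the anticoagulant affects the measured value, for instance because a liquid additive dilutes the plasma, part of the difference between women reflects the tube. With similar use in both groups this is extra noise. With different use it becomes a group difference that the planned tests cannot tell from disease. It cannot be corrected later unless the tube was recorded. Recruitment began on April 1, 2025.

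**Working it through.** **Inputs from the Power and Data and Statistical Analysis sections.** 20 cases and 20 controls; coefficient of variation (CV) 30%; 80% power for a 27% change; two-tailed tests. Alpha is not stated, so 0.05 is assumed.

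**Step 1: the plan's own figure.** The standardized difference is 0.27/0.30 = 0.90. For the unpaired two-sided test with 20 per group, the noncentrality is 0.90 × √(20/2) = 2.85.

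- Normal approximation: power 81.2%.
- Exact t test: power 79.2%. The change detectable with 80% power is 27.3%.

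The stated 27% reproduces, so the point does not rest on an error in it.

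**Step 2: size of a dilution effect.** The documents give none. Assume 1 part liquid citrate to 9 parts blood, and haematocrit (Hct) 0.30 to 0.40. The diluted fraction is 1 − 9(1 − Hct)/[9(1 − Hct) + 1].

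| Hct | Calculation | Dilution |
|---|---|---|
| 0.30 | 1 − 6.30/7.30 | 13.7% |
| 0.35 | 1 − 5.85/6.85 | 14.6% |
| 0.40 | 1 − 5.40/6.40 | 15.6% |

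The middle value is 14.6/27 = 54% of the detectable change.

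**Step 3: false-positive rate with no true difference.** 40,000 simulated studies per row, 20 women per group, log SD √ln(1 + 0.30²) = 0.2936, unpaired two-sided t test. Values in citrate tubes are shifted by ln(1 − 0.146) = −0.158.

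| Citrate in cases | Citrate in controls | Cases appear | False-positive rate |
|---|---|---|---|
| 50% | 50% | unchanged | about 4% |
| 40% | 60% | 3% higher | about 5.5% |
| 35% | 65% | 5% higher | about 7% |
| 0% | 25% | 4% higher | about 7% |
| 0% | 50% | 8% higher | about 12% |
| 0% | 100% | 17% higher | about 38% |

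Swapping the groups leaves the rates the same and reverses the direction: cases then appear about 8% lower (50% against 0%) or 15% lower (100% against 0%). At CV 20% the last two rates are 21% and 69%; at CV 40% they are 9% and 24%.

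**Step 4: cost of balanced use.** With a tube effect b and a 50/50 split in both groups, the variance becomes 0.30² + b²/4 and there is no bias. Power at a 27% change falls from 79.2% to 78.9%, 78.1%, 74.9% and 69.9% for assumed effects b of 5%, 10%, 20% and 30%. For the 14.6% dilution on the log scale, it falls from 71% to 68%.

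**The case against.** **Serum against plasma.** Serum appears only in overview text. Every operational step uses plasma, and all the named tubes contain an anticoagulant, so none would yield serum. This stands: it is loose wording, not evidence that two matrices will be measured.

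**Tube use by group.** A reader might infer that tube choice follows case status, because cases come from clinics and wards and controls from clinic lists. The documents do not support that. Controls are concurrent and from the same antenatal clinic, and no passage links the tube to ward or diagnosis. The 12% and 38% figures describe chosen scenarios. They do not predict what this study will show.

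**Direction.** A reader might also infer that the artefact would imitate the general elevation that the study expects. That holds only if controls receive more citrate; the reverse would hide an elevation. A common direction for all metabolites follows from dilution, but the documents do not establish it for other differences between anticoagulants.

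**Condensed method and pilot aims.** The laboratory section presents itself as a brief account, so the working procedure may already fix one tube. The study is also a pilot, focused on description and precision. Both points lower the urgency. Neither removes the conflict, because the article states two different instructions and leaves one of them open; this is not a detail merely left out.

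**Conclusion.** The point holds as a contradiction in the collection instructions, with an anticoagulant left open and uncontrolled. That much is certain from the text.

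The consequence is conditional. Balanced use brings no bias and a modest loss of power, for example from 79% to 75% under an assumed 20% tube effect. Unbalanced use biases the comparison in either direction. With an assumed 1:9 citrate tube, the false-positive rate at CV 30% runs from about 5% near balance, through about 12%, to 38% at complete imbalance. These figures rest on the assumed citrate ratio and haematocrit, an assumed alpha of 0.05, and splits that the documents do not report.

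It would go too far to say that samples already collected are not comparable, or that the comparison is biased. The documents say only that recruitment has started, not which tubes were used.

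**What to change.** 1. Name one anticoagulant tube for all 40 women, in identical words in Recruitment and Blood Metabolite Analysis, and delete the either/or. This also gives each case and her matched control the same tube.
2. Replace serum with plasma in the abstract and in Aims of This Study, as a wording correction.
3. Record the tube type for every sample already taken.
4. If more than one type was used, report tube type by group and add a sensitivity analysis. It should be restricted to tube-concordant samples, or adjusted for tube only where both tubes occur in both groups. Under complete imbalance, adjustment cannot separate tube from disease.

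The cost is a few words, one collection instruction and one recorded item. The sample size and the stated 27% do not change. The downside is that a few early samples may drop out of the sensitivity analysis. If many pairs proved discordant, the loss of precision with only 20 per group would be larger and should be reported.

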### Trophoblast Growth and Treatments

First, human placental–derived choriocarcinoma trophoblastic (BeWo) cells will be obtained from the American Type Culture Collection. In the unlikely event that this cell line is ineffective, others are available for investigation. The cells are cultured in Dulbecco’s modified Eagle’s medium/12 Ham’s media (Sigma; catalog number D8437; 500 ml) supplemented with 10% fetal bovine serum (Sigma; catalog number F9665; 500 ml) and 1% penicillin streptomycin (Sigma; catalog number P4333; 100 ml). A total of 1 × 10^6^ cells are dispensed into a culture flask, and the cells are incubated at 37 °C in a 5% CO_2_ incubator for cellular attachment.

The first set of treatments will involve a solvent control and cells subjected to hypoxia, hCG supplementation (obtained from ProspecBio; catalog number HOR-250; 5 mg), or both to stimulate syncytialization. Cytotoxicity assays will be carried out as described below. The second set of treatments will involve addition of the abovementioned harmful metabolites at a range of concentrations and screened for cytotoxicity. Cells showing evidence of stress in microscopy will be tested for cytotoxicity, apoptosis, and energy metabolism, as described below. In such cases, the culture medium will be used for metabolite screening, as outlined above. The cells will be harvested to determine the expression level of 7 key genes, as described below, and stored frozen for transcriptomic analysis in a future project.

### Trophoblast Cell Studies

Cell viability will be determined using a standard MTT (3-(4,5-dimethylthiazol-2-yl)-2,5-diphenyltetrazolium bromide) assay kit (Abcam, catalog number ab197010; 250 tests) [26] according to the manufacturer’s protocol. Energy metabolism will be studied by measuring glucose uptake and the adenosine diphosphate (ADP) to adenosine triphosphate (ATP) ratio, as described previously in the literature [27]. Given the known elevated expression of a membrane scramblase in the placenta of patients with preeclampsia [9], apoptosis and necrosis will be assessed using the Annexin V-FITC kit (Beckman Coulter), according to the manufacturer’s instructions. Analysis will be performed using a BD FACsAria flow cytometer, collecting a total of 100,000 events. For cultures that appear stressed, metabolite concentrations will be determined by extracting metabolites from the culture medium and analyzing them with HPLC/MS in the same way as described above for the plasma samples.

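### Culture-medium metabolites are measured only where cells look stressed, so a condition that raises metabolites without visible stress would be missed and a negative result would not rule it out

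*Protocol article*

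**What the plan says.** The protocol article describes two sets of treatments under Trophoblast Growth and Treatments. On the first it says: "The first set of treatments will involve a solvent control and cells subjected to hypoxia, hCG supplementation", or both together. On cytotoxicity in that set it adds, without condition: "Cytotoxicity assays will be carried out as described below". The second set is the "addition of the abovementioned harmful metabolites at a range of concentrations and screened for cytotoxicity".

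The same section then makes further testing depend on appearance: "Cells showing evidence of stress in microscopy will be tested for cytotoxicity, apoptosis, and energy metabolism, as described below". It continues: "In such cases, the culture medium will be used for metabolite screening, as outlined above". Trophoblast Cell Studies repeats the condition for the metabolites: "For cultures that appear stressed, metabolite concentrations will be determined by extracting metabolites from the culture medium". That section describes the viability, energy and apoptosis assays without repeating it.

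Data and Statistical Analysis carries the patient tests (t tests, or Mann-Whitney if the data are not normal) over to the cultures: "These same tests will be used for metabolite concentrations in the in vitro cell cultures".

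**The concern.** The metabolite readout is what the in vitro work is for. Aims of This Study asks whether the harmful metabolites turn up in the medium, and the third objective asks which conditions set off CoA restriction. A rule that reads the medium only after the cells look unwell decides which conditions can give an answer, and it does so on something observed after treatment. No criterion for stress is stated.

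Two things are at stake:

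- **Missed conditions.** A condition that raises the metabolites before, or without, visible damage yields no metabolite measurement.
- **A selected comparison.** If treated cultures are read only when stressed while controls are read regardless, the two groups have not been chosen in the same way. A difference can then arise from the selection alone.

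**Working it through.** **1. Which readouts are conditional.** Setting the two laboratory sections side by side:

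| Readout | Trophoblast Growth and Treatments | Trophoblast Cell Studies |
|---|---|---|
| Cytotoxicity / viability | Ordered unconditionally for set 1 and as a screen across concentrations in set 2, but also listed among the tests for stressed cells | No condition |
| Apoptosis | Only if stress is seen | No condition |
| Energy metabolism | Only if stress is seen | No condition |
| Metabolites in medium | Only if stress is seen | Only if the culture appears stressed |
| Seven-gene expression | Cells harvested; unclear whether the condition applies | Not covered |

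The condition is stated in both sections for metabolites, in one of the two for apoptosis and energy metabolism, and inconsistently for cytotoxicity.

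**2. Whether "stressed" could just mean "treated".** Aims of This Study does speak of stressing the cells. But the two conditional sentences refer to evidence under the microscope and to how cultures appear. That is an observed response, not an assigned arm.

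**3. What follows for a negative result.** Suppose a condition raises metabolites and the cells look normal. Under the rule its medium is not analysed. Limitations says that if the cultures do not show raised metabolites, the work still excludes some possibilities. It cannot exclude a condition for which no metabolite value exists.

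**4. What follows for the comparison.** The plan gives no replicate number, power figure or detectable difference for the cultures, so there is no planned figure to reproduce. The Power section's 27% change at 80% power concerns 20 against 20 women and plays no part here. The following is an illustration only.

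Assumptions, none from the documents: log metabolite level and a latent stress score are standard normal with correlation r; treatment has no true effect; a fraction f of treated cultures looks stressed and only those are read; controls are read without selection; 6 cultures per group; unpaired t test, two-sided 5%.

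The selected treated mean is shifted by r × φ(z)/f standard deviations, where z cuts off the upper fraction f:

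- f = 0.25: φ(0.674)/0.25 = 0.318/0.25 = 1.27, so the shift is 0.38 SD at r = 0.3 and 0.89 SD at r = 0.7.
- f = 0.50: φ(0)/0.50 = 0.399/0.50 = 0.80, so the shift is 0.24 SD at r = 0.3 and 0.56 SD at r = 0.7.
- f = 0.75: 0.318/0.75 = 0.42, so the shift is 0.13 SD at r = 0.3 and 0.30 SD at r = 0.7.

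Simulated false-positive rates (20,000 comparisons per cell):

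| r | f = 0.25 | f = 0.50 | f = 0.75 |
|---|---|---|---|
| 0 | 4.9% | 4.7% | 4.7% |
| 0.3 | 9.1% | 6.6% | 5.6% |
| 0.5 | 18.4% | 10.1% | 6.4% |
| 0.7 | 34.1% | 15.0% | 7.5% |

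With no correlation there is no bias. With correlation, the bias grows as fewer cultures pass the visual check.

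**The case against.** The best defence is that this is an ordinary screening cascade in the laboratory arm of a pilot: look first, then spend the expensive assays where something is happening. Several stronger readings that a reader might infer also fail on the text.

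- *Unstressed cultures get no cell-status reading at all.* Not so. The Figure 2 legend counts cytotoxicity as cell status, and cytotoxicity is ordered without the condition in both sets.
- *Solvent controls are never measured.* This goes too far. The Figure 2 legend has control material entering the laboratory techniques, and two-group tests need a comparator. Controls are probably intended; the methods text just does not say so.
- *Gene expression is lost too.* The text is unclear, and Gene Expression Profiling speaks only of cells after treatment.
- *Stress is itself the outcome, so the results are biased.* Stress is a selection variable. Bias depends on its correlation with the metabolites, which the documents do not give. The calculation also assumes selection culture by culture; if whole conditions are taken forward, its figures do not apply as they stand.
- *Medium readings merely reflect what was put in.* Serum is in all cultures and is a common background. The added dose matters only in the second set, and there only for the metabolite added. The article nowhere says that this metabolite will be counted as a response in its own arm.
- *Too few replicates for a rank test, or the wrong model for the first set.* Replicate numbers are not stated, and the choice of a factorial or dose-trend model is an analysis preference. Neither bears on the visible-stress rule.

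These objections narrow the point but do not remove it. The condition on metabolites is a positive rule stated in two sections, not a detail dropped in condensing. A cascade that reads metabolites only after visible stress does not fit an objective about what initiates the process, whether selection is by flask or by condition.

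**Conclusion.** The point holds in a limited form. Metabolite measurement is confined to cultures that look stressed, with no criterion for stress and no explicit provision for unstressed or solvent-control medium. One section confines apoptosis and energy metabolism in the same way. Cytotoxicity is screened in all cultures, although the text contradicts itself on this.

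The firm consequence needs no assumption: a condition without visible stress has no metabolite reading, so a negative finding does not rule it out. The second consequence, a distorted comparison, is conditional. It requires stress and metabolite levels to be correlated and treated cultures to be selected while controls are not. Its size is unknown; the range of about 6% to 34% false positives belongs to the assumed inputs only. Because the study's own hypothesis links these metabolites to cell harm, zero correlation is not a safe assumption.

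This affects one of three objectives. No figure stated in the article changes, and the comparison between women with preeclampsia and controls is untouched.

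**What to change.** Remove the visible-stress condition from both sections and reconcile the two statements on cytotoxicity. Then state that:

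- metabolites, apoptosis and energy metabolism are measured in every first-set arm: solvent control, hypoxia, hCG, and both;
- in the second set they are measured in the solvent control and at the tested concentrations, or in a subset fixed in advance without regard to microscopy;
- microscopic stress is recorded and reported as a readout in its own right;
- in the second set, the medium level of the metabolite that was added is not interpreted as a cell response unless compared with a cell-free medium blank;
- the seven-gene assay is, or is not, subject to any selection.

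The cost is more HPLC/MS, flow cytometry and energy-assay runs, plus a few blanks. The extra load could be appreciable across five metabolites at several concentrations, which is why a prespecified subset is acceptable. Apart from the blanks, the assays are those already described, and no additional patients are needed. The article reports that the cell culture was still being optimised and that data analysis had not begun, so the change can still be made.

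### Medium metabolites are tested as concentrations with no stated cell-free baseline or cell-number denominator, so loss of living cells alone can raise medium leucine

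*Protocol article*

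**What the plan says.** Aims of This Study describes three ways of investigating the stressed trophoblasts. On the medium it says: "The first will determine if the harmful metabolites appear in the cell culture medium". Limitations expects the cultures to show elevated levels of these metabolites, and Objectives uses the cell work to find which conditions start CoA restriction.

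Trophoblast Growth and Treatments gives the set-up. The medium is "supplemented with 10% fetal bovine serum". One million "cells are dispensed into a culture flask, and the cells are incubated at 37 °C"; no count at harvest is stated. On the treatments: "The first set of treatments will involve a solvent control and cells subjected to hypoxia", hCG, or both. The second set adds the harmful metabolites themselves over a range of concentrations. Selection for further work is by appearance: "Cells showing evidence of stress in microscopy will be tested for cytotoxicity, apoptosis, and energy metabolism, as described below". The medium of those cultures then goes to metabolite screening.

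Trophoblast Cell Studies says how the medium is read: "metabolite concentrations will be determined by extracting metabolites from the culture medium and analyzing them with HPLC/MS in the same way" as for plasma. Data and Statistical Analysis names what is tested: "These same tests will be used for metabolite concentrations in the in vitro cell cultures". Viability is measured by MTT, but the text does not link it to the metabolite result.

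**The concern.** A plasma concentration can be compared between women as it stands. A medium concentration depends on what was in the medium at the start, how many cells were alive and for how long, and what each cell did. Only the last bears on the hypothesis.

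Leucine shows the problem most clearly. Human cells cannot make it, so a growth medium has to supply it, and over an incubation the cells draw it down on balance. (This is general biochemistry; the article does not give the leucine content of the medium.) The proposed mechanism is interrupted breakdown of branched-chain amino acids, so each cell would use less leucine. Having fewer living cells also leaves more leucine behind. Both raise the medium level, and the concentration alone cannot tell them apart. Because cultures are screened for looking stressed, a loss of living cells relative to the control is plausible.

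Two related problems follow. In the second treatment set, the value for an added metabolite includes the dose. For a metabolite that cells release, fewer cells release less, so a real rise per cell can be hidden.

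**Working it through.** **The plan's own figure.** The article gives no effect size or replicate number for the cultures. Its only detectable change is the 27% in the Power section. With 20 per group, a coefficient of variation of 30%, 80% power and an assumed two-sided alpha of 0.05, the minimum standardised difference is 0.909, and 0.909 × 30% = 27.3%, so it reproduces. It concerns plasma and is not used as a yardstick here.

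**Inputs for leucine, all assumed.** Set the starting concentration to 1.
- c: fraction of the leucine that the control culture uses.
- v: living-cell time in the treated culture, relative to control.
- Uptake per cell is the same in both cultures.

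**Formula.** Control medium ends at 1 − c and treated medium at 1 − c·v.

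Apparent rise = (1 − c·v)/(1 − c) − 1

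| c | v = 0.8 | v = 0.5 | v = 0.3 |
|---|---|---|---|
| 0.05 | 1.1% | 2.6% | 3.7% |
| 0.1 | 2.2% | 5.6% | 7.8% |
| 0.2 | 5.0% | 12.5% | 17.5% |
| 0.4 | 13.3% | 33.3% | 46.7% |
| 0.6 | 30.0% | 75.0% | 105.0% |

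For example, c = 0.4 and v = 0.5 give (1 − 0.20)/(1 − 0.40) − 1 = 0.80/0.60 − 1 = 33.3%. The rise is positive whenever c > 0 and v < 1. It vanishes if uptake per cell increases by 1/v, which is 2-fold at v = 0.5.

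**With a blank and a denominator.** Net consumption against the blank is c in the control and c·v in the treated culture. Divided by living-cell time (1 and v), both equal c, so the artefact is 0 under the same assumptions.

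**Why end-point viability is a weak denominator.** Suppose half the cells die just before harvest. Consumption is still about c. Dividing by the end-point value 0.5 gives 2c, a false doubling in the direction opposite to the hypothesis. Using the mean of start and end, (1 + 0.5)/2 = 0.75, gives c/0.75 = 1.33c. If the loss is instead linear over the incubation, consumption is 0.75c and the mean gives 0.75c/0.75 = c, which is correct.

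**Released metabolites.** With a negligible baseline and release per cell multiplied by k, the treated-to-control ratio is k·v. At k = 2 and v = 0.5 it is 1, so a true doubling per cell shows as no change.

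**Added metabolites.** The medium value is baseline + dose + net cell contribution. Without a dosed blank, the last term cannot be isolated.

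**The case against.** The strongest reply is that this is a condensed article. A full protocol (version 1.1) is cited but not shown, and blanks and normalisation are bench details that an article may leave out. That is fair as far as it goes: one can say only that the article states neither, not that the laboratory will use neither. It does not settle the matter. The article names the tested variable as concentration and the reading as appearance in the medium. A net change per cell is a different variable, so the statistical text would still need to change.

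Second, the size is unanchored. Neither c nor v is in the document, and at 5% to 10% consumption with v between 0.8 and 0.5 the rise is only about 1% to 6%. Cells could also raise their uptake. This stands, and it limits the claim to what can happen.

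A reader might go further and infer any of the following. The document supports none of them.
- *Stressed cultures are bound to show raised leucine.* That depends on the unknown c, v and uptake per cell.
- *Viability differs between arms by design.* Hypoxia and hCG are given to stimulate syncytialization, and cytotoxicity is an outcome. Selection for stress makes cell loss plausible, not certain.
- *Any toxic condition would be declared CoA restriction.* Four other metabolites, seven genes, and the apoptosis and energy assays are also read, and no rule makes leucine decisive. For released products the bias runs the other way.
- *The artefact exceeds what the study is powered for.* The 27% belongs to the comparison of women.

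**Conclusion.** The point holds in a limited form. As written, the in vitro comparison tests medium concentrations from stressed-looking cultures in serum-supplemented medium, with no stated baseline or cell-number denominator. For leucine, cell loss can imitate the predicted effect. The illustrated range is about 1% to about 105%, assuming equal uptake per cell and net consumption by the cells; the true value cannot be fixed from the document. Where metabolites are added, their measured value also contains the dose, which needs no assumption about c or v.

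This should be corrected because the culture work is one of the study's two lines of evidence. It does not touch the comparison of patients with controls, and it does not show that the culture work must mislead.

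**What to change.** 1. Trophoblast Growth and Treatments: in each run, incubate and assay a cell-free complete-medium blank for every condition, including hypoxia, hCG, both, and each metabolite at each added concentration. State that solvent-control medium is assayed alongside the stressed cultures.
2. Data and Statistical Analysis: make the tested variable the net change from the matched blank, divided by a cell-number measure that does not depend on metabolism (cell count, DNA or protein), ideally averaged over the start and end of incubation. Do not rely on end-point MTT alone: it reflects cell metabolism, which CoA restriction is expected to disturb, and consumption builds up over the whole incubation. Report the unadjusted concentration as well.
3. Aims of This Study: describe the leucine signal as reduced net consumption per cell, not as appearance in the medium.

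The cost is a few extra injections per run, a simple count, and some added noise from subtracting and dividing measured quantities. Averaging start and end reduces the timing error in the denominator but does not remove it.
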